### Procedures

The details about the measurements, study tools, and timelines are outlined in Table 1.

**Table 1 table1:** Measurements, study tools, and study timeline.

Variables	Components	Study tools	Baseline		8 weeks
Study feasibility	Response rate, screening yield, enrollment rate, time to enrollment, intervention compliance, resource use, and retention rate	REDCap^a^ database	✓		✓
Intervention feasibility	Qualitative and quantitative research	Feasibility of Intervention Measure [46]	✓		✓
Intervention feasibility	Qualitative and quantitative research	In-depth interviews	✓		✓
Intervention acceptability	Qualitative and quantitative research	Theoretical Framework of Acceptability questionnaire [47]	✓		✓
Intervention acceptability	Qualitative and quantitative research	In-depth interviews	✓		✓
Intervention appropriateness	Qualitative and quantitative research	Intervention Appropriate Measure [46]	✓		✓
Intervention appropriateness	Qualitative and quantitative research	In-depth interviews	✓		✓
Participants’ expectations of and experiences with the intervention	Qualitative research	In-depth interviews	✓		✓
Sociodemographics	Age, sex, marital status, education, and occupation	WHO STEPS^b^ [34] and NHANES^c^ questionnaires [35]	✓		x^c^
Eligibility criteria	Inclusion and exclusion criteria^e^	Short-form IPAQ^f^ [32]	✓		x
Behavioral measures	Dietary habits	ASA24^g^ dietary assessment tool [36]	✓^h^	✓^h^	
Behavioral measures	Physical activity	Short-form IPAQ [32]	✓^i^	✓^i^	
Behavioral measures	Smoking	WHO STEPS [34] and NHANES questionnaires [35]	✓		✓
Behavioral measures	Alcohol consumption	WHO STEPS [34] and NHANES questionnaires [35]	✓		✓
Physical measures	Height	Stadiometer	✓		x
Physical measures	Weight	Digital weighing scale	✓		✓
Physical measures	Waist circumference	Inelastic measuring tape	✓		✓
Physical measures	Hip circumference	Inelastic measuring tape	✓		✓
Physical measures	BP^j^	DINAMAP BP apparatus	✓		✓
Physical measures	Body composition	Bioimpedance analysis	✓		✓
Biochemical measures	OGTT^k^ (0, 30, and 120 minutes)	Enzymatic assays	✓		✓
Biochemical measures	Insulin levels at 0 and 30 minutes	Immunoassays	✓		✓
CGM^k^	Proportion of time and mean time spent in nocturnal (00:00-06:00) normoglycemia (60 to <100 mg/dl) [48]	Dexcom G6 Pro (DexCom, Inc)	✓^l^	✓^l^	

^a^REDCap: Research Electronic Data Capture.

^b^WHO STEPS: World Health Organization STEPwise approach to noncommunicable disease risk factor surveillance.

^c^NHANES: National Health and Nutrition Examination Survey.

^d^x: the particular variable will not be collected during that particular timepoint.

^e^Inclusion criteria: aged 35-65 years, overweight or obese (body mass index ≥25 kg/m² [≥23 kg/m² if Asian descent]), physically inactive (less than 150 minutes per week of moderate-intensity physical activity and less than 75 minutes per week of vigorous-intensity physical activity and <600 metabolic equivalent task–minutes per week), and a diagnosis of isolated impaired fasting glucose (fasting plasma glucose 100-125 mg/dL and 2-hour plasma glucose<140 mg/dL). Exclusion criteria: diagnosis of diabetes, diagnosis of other chronic illnesses (eg, cardiovascular disease, stroke), current smoker, history of anemia, currently enrolled in weight loss programs, currently enrolled in any regular exercise programs, currently following a specific diet (eg, ketogenic diet, Mediterranean diet), currently taking weight-loss medications or drugs known to influence glucose tolerance (steroids and antipsychotics), currently taking beta-blockers or calcium channel blockers, underwent bariatric surgery or plans to undergo the surgery during the study period, plans to relocate outside the study area during the study period, pregnant, or breastfeeding.

^f^IPAQ: International Physical Activity Questionnaire.

^g^ASA24: Automated Self-Administered 24-Hour Dietary Assessment Tool.

^h^Dietary habits will be assessed biweekly throughout the study duration.

^i^Physical activity of control participants will be assessed biweekly throughout the study duration.

^j^BP: blood pressure.

^k^OGTT: oral glucose tolerance test.

^l^All participants will be fitted with the continuous glucose monitoring device 10 days before the intervention, and they will be trained to replace the device every 10 days until 10 days post intervention.

### Study Feasibility

Table 2 shows the study feasibility metrics. Continuous data collection on feasibility parameters, such as response rate, screening yield, enrollment rate, time to enrollment, intervention compliance, resource use (cost and staff time), and retention rate, will be conducted throughout the study.

**Table 2 table2:** Study feasibility metrics.

Parameters	Calculations
Response rate	Number of individuals responded to the invitation/number of individuals invited
Screening yield	Number of individuals diagnosed with i-IFGa/number of individuals screened
Enrollment rate	Number of individuals enrolled/number of individuals diagnosed with i-IFG
Time to enrollment	Average time taken from sending the invitation to enrolling one participant in the trial
Intervention compliance	Number of HIITb sessions attended/Total number of HIIT sessions
Resource use	Program costs: Includes screening cost, cost of procedures, intervention cost, participant incentives, and other costs. Staff time: Time spent screening and recruiting participants, time spent delivering the intervention, time spent making phone calls to participants, time spent implementing the study procedures, and time spent on baseline and follow-up assessments.
Retention rate	Number of participants attended follow-up visits/number of participants enrolled

^a^i-IFG: isolated impaired fasting glucose.

^b^HIIT: high-intensity interval training.

### Intervention, Feasibility, Acceptability, and Appropriateness

The Feasibility of Intervention Measure (FIM) will evaluate the feasibility of the intervention, encompassing questions regarding its implementability, possibility, doability, and ease of use [46]. The acceptability of the intervention will be assessed through the Theoretical Framework of Acceptability (TFA) questionnaire, which explores affective attitude, burden, ethicality, perceived effectiveness, intervention coherence, self-efficacy, opportunity costs, and general acceptability [47]. The Intervention Appropriate Measure (IAM) will evaluate the appropriateness of the intervention, including questions about its fittingness, suitability, applicability, and alignment with participants’ needs [46]. Responses to the questions in all 3 questionnaires will be recorded on a Likert scale of 1 to 5. The mean total score for each of these scales will be calculated by combining the individual Likert points of each scale. Higher scores on the FIM, TFA, and IAM scales indicate greater feasibility, acceptability, and appropriateness, respectively, among participants.

### Continuous Glucose Monitoring

By providing 288 glucose measurements per day throughout the 8-week intervention and 10-day follow-up, continuous glucose monitoring (CGM) can track the dynamic changes in fasting glucose levels induced by HIIT [48]. This can help identify when the effects of HIIT on fasting glucose levels become evident and whether these effects are sustained after the intervention, which may not be captured by a single blood glucose measurement taken after 8 weeks. All participants, regardless of their assigned treatment, will be fitted with a CGM device on their abdominal area upon enrollment. The CGM device, Dexcom G6 Pro CGM system (DexCom, Inc), will be used in blinded mode to minimize bias and ensure that it does not influence the study outcomes. Participants will be instructed to eat their last meal by 10 PM daily after the CGM fitting. They will wear CGM devices for approximately 80 days, including 10 days prior to the intervention, the 8-week intervention period, and 10 days following the intervention. Participants will be trained on how to replace the device every 10 days, using the instructions provided in the manual [49], during the first study visit. The adequacy of CGM data will be evaluated using the following criteria: a minimum of 80% of the potential 288 glucose values per day should be present for any 7 consecutive days, commencing from the day following sensor insertion [50].

### Clinical Measures

Data on health behaviors, physical measurements, and biochemical measurements will be collected at both baseline and 8 weeks.

#### Health Behaviors

Physical activity levels will be assessed using the short form of IPAQ [32] and dietary intake with the Automated Self-Administered 24-Hour Dietary Assessment Tool questionnaire [36]. Data on smoking and alcohol use will be obtained using questions adapted from the WHO STEPS [34] and the National Health and Nutrition Examination Survey questionnaires [35].

#### Physical Measures

Physical measurements will be taken following standard protocols [37,51]. Height will be measured using a stadiometer (Welch Ally—Scale-Tronix) with an accuracy of 0.1 cm. Weight will be assessed using a digital weighing scale (Welch Ally—Scale-Tronix) with precision to the nearest 0.1 kg. Waist and hip circumferences will be measured using an inelastic measuring tape (BaumGartens) with a precision of 0.1 cm. Blood pressure will be measured using the DINAMAP automatic blood pressure apparatus (GE HealthCare). Body composition measures, including fat mass, muscle mass, fat-free mass, visceral adipose tissue mass, and fat percent, will be obtained using the bioimpedance analysis.

#### Biochemical Measures

Participants will undergo an OGTT following standard protocols [52,53]. The test will be conducted after an overnight fast of at least 10 hours, with the session scheduled between 7 and 9 AM. Venous blood samples will be collected at 0, 30, and 120 minutes after ingesting a 75-g oral glucose load dissolved in 250-300 mL of water, consumed over 5 minutes. Additionally, blood samples for insulin will be obtained at 0 and 30 minutes after glucose load ingestion. Blood samples will be processed and analyzed at the Emory Medical Laboratory (EML). EML is a fully accredited and licensed clinical laboratory, actively participating in the College of American Pathologists Laboratory Accreditation Program. Additionally, it holds Clinical Laboratory Improvement Amendments certification through the Centers for Medicare and Medicaid Services. EML is also duly licensed by the state of Georgia. Glucose levels will be assessed through enzymatic assays and insulin levels via immunoassays based on the EML protocol [53]. All these analyses will use kits provided by Beckman Coulter Inc and will be performed on a Beckman Coulter analyzer.

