**Insulin resistance**			
	Whole-body insulin sensitivity	Matsuda index [57]	10,000 /√((G_0_×I_0_)×(G_mean_^i^×I_mean_^j^))
	Insulin resistance	HOMA-IR^k^ [56]	(I_0_×G_0_)/22.5 I0 in µU/L G0 in mmol/l
	Hepatic insulin resistance	HIRI^l^ [58]	(G_0_–G_30_[AUC^m^]×I_0_-_30_[AUC]) G0 in mg/dl I0 in µU/ml
	Muscle insulin resistance	MISI^n^ [58]	(dG/dt^o^)/Ī^p^

^a^IR: insulin resistance.

^b^IGI: insulinogenic index.

^c^I_30_: mean insulin at 30 minutes during the oral glucose tolerance test.

^d^I_0_: mean insulin at 0 minutes during the oral glucose tolerance test.

^e^G_30_: mean glucose at 30 minutes during the oral glucose tolerance test.

^f^G_0_: mean glucose at 0 minutes during the oral glucose tolerance test.

^g^DI_O_: oral disposition index.

^h^HOMA-B: homeostatic model assessment of ß cell function.

^i^G_mean_: mean glucose during the 2-hour oral glucose tolerance test.

^j^I_mean_: mean insulin during the 2-hour oral glucose tolerance test.

^k^HOMA-IR: homeostatic model assessment of insulin resistance.

^l^HIRI: hepatic insulin resistance index.

^m^AUC: area under the curve during the first 30 minutes of the oral glucose tolerance test.

^n^MISI: muscle insulin sensitivity index.

^o^dG/dt: slope of the regression line from the peak of the plasma glucose curve to its nadir (mmol/L/min).

^p^Ī: mean insulin concentration over the 2-hour duration of the oral glucose tolerance test (pmol/L).

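### Insulin is scheduled only at 0 and 30 minutes, so two of the seven Table 3 indices (Matsuda and muscle insulin sensitivity) cannot be computed as defined

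*Protocol article*

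**What the plan says.** On sampling, Biochemical Measures states: "Venous blood samples will be collected at 0, 30, and 120 minutes after ingesting a 75-g oral glucose load". It then adds that "blood samples for insulin will be obtained at 0 and 30 minutes after glucose load ingestion". Table 1 (Procedures) keeps the two apart. The glucose tolerance test row is timed at "0, 30, and 120 minutes" and uses enzymatic assays; a separate row reads "Insulin levels at 0 and 30 minutes" and uses immunoassays. Biochemical Measures confirms which assay belongs to which analyte: "Glucose levels will be assessed through enzymatic assays and insulin levels via immunoassays".

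On the indices, Table 3 lists seven. The Matsuda formula uses a mean insulin that its footnote defines as "mean insulin during the 2-hour oral glucose tolerance test". MISI divides a glucose slope by "mean insulin concentration over the 2-hour duration of the oral glucose tolerance test", and the slope is the "slope of the regression line from the peak of the plasma glucose curve to its nadir".

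Secondary Outcomes lists between-group differences in change in these indices from baseline to 8 weeks. Statistical Analysis (Objective 2) also correlates changes in the indices with changes in fasting glucose.

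**The concern.** The sampling schedule and the index definitions do not fit each other. Matsuda and MISI both need insulin across two hours, and the last insulin sample is at 30 minutes. The article gives no modified version of either index for a 0 and 30 minute schedule. A statistical analysis plan could not repair this later, because it cannot recover insulin that was never assayed.

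At stake are two named secondary outcomes: one of the two whole-body measures, and the only muscle-specific measure. If the visits run as written, the indices must either be left out or be replaced by a different quantity.

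Table 3 also has a smaller inconsistency. Insulin is in µU/l for the oral disposition index, HOMA-B and HOMA-IR, but in µU/ml for the hepatic index.

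**Working it through.** The plan states no figure to reproduce here. The check sets each Table 3 formula against the schedule.

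**1. Insulin needed by each index**

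| Index | Insulin needed | Computable from 0 and 30 min? |
|---|---|---|
| Insulinogenic index | 0, 30 | yes |
| Oral disposition index | 0, 30 | yes |
| HOMA-B | 0 | yes |
| HOMA-IR | 0 | yes |
| Hepatic index | 0-30 area | yes |
| Matsuda | 2-hour mean | no |
| MISI | 2-hour mean | no |

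**2. Share of the window without insulin.** (120 − 30)/120 = 90/120 = 75%.

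**3. Weight of the missing value.** If the 2-hour mean is a trapezoid over 0, 30 and 120 minutes (an assumption; Table 3 gives no averaging rule), then

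I_mean = [30(I0 + I30)/2 + 90(I30 + I120)/2]/120 = 0.125·I0 + 0.5·I30 + 0.375·I120.

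The unmeasured 120-minute value carries weight 0.375.

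**4. Illustration that 0 and 30 minute data do not determine the index.** Every value here is assumed and none is in the documents: I0 = 12 and I30 = 70 µU/mL; glucose 108, 165 and 120 mg/dL; I120 from 20 to 100 µU/mL. The 0/30 average is (12 + 70)/2 = 41.0. For given glucose values Matsuda varies as 1/√I_mean and MISI as 1/I_mean, so using 41.0 in place of the three-point mean changes them by √(I_mean/41) − 1 and I_mean/41 − 1.

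| I120 | Averaging rule | I_mean | Change in Matsuda | Change in MISI |
|---|---|---|---|---|
| 20 | trapezoid | 1.5 + 35 + 7.5 = 44.0 | +4% | +7% |
| 100 | trapezoid | 1.5 + 35 + 37.5 = 74.0 | +34% | +80% |
| 20 | simple mean | 102/3 = 34.0 | −9% | −17% |
| 100 | simple mean | 182/3 = 60.7 | +22% | +48% |

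Both the size and the sign depend on the unmeasured value and on the averaging rule. The table shows that the index is undetermined; it does not estimate a bias.

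**5. MISI slope.** Glucose is available at three times. With the peak at 30 and the nadir at 120 minutes, the regression reduces to (G30 − G120)/90, a line through two points. A peak between 30 and 120 minutes is not seen. If G120 ≥ G30, there is no fall after 30 minutes to measure. An insulin assay at 120 minutes supplies the denominator but does not improve this numerator.

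**6. Units.** HOMA-IR is I0 × G0/22.5. With assumed I0 = 10 µU/mL and G0 = 6 mmol/L it is 10 × 6/22.5 = 2.67; with the same insulin entered in µU/L it is 10,000 × 6/22.5 = 2,667, a factor of 1,000. HOMA-B is proportional to I0 and changes by the same factor. In the oral disposition index insulin appears in both numerator and denominator, so its unit cancels.

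**The case against.** **The 120-minute sample might include insulin.** The sentence on venous samples could be read that way, but the next sentence and the separate Table 1 row limit insulin to 0 and 30 minutes. This reading fails.

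**The two available samples could simply be averaged.** That is a 0-30 minute mean, not the quantity Table 3 defines. A reader might infer that the investigators intend such a substitute under the published name; nothing in the article says so.

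**The indices matter little here.** Much of this stands. Primary outcomes are feasibility and acceptability, and efficacy is called preliminary. The Introduction attributes hepatic insulin resistance and impaired early-phase secretion to isolated impaired fasting glucose, and skeletal-muscle resistance to isolated impaired glucose tolerance. The insulinogenic and hepatic indices, which address the first pair, can be computed, and HOMA-IR still gives a whole-body measure. A reader might infer that the mechanistic objective fails altogether; the documents do not support that.

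**A two-point slope is still a slope.** This stands in part. Table 3 sets no minimum number of points, so with 120-minute insulin a coarse MISI is defined whenever glucose falls after 30 minutes. Keeping it with a clear label is a legitimate alternative to dropping it.

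**The unit mismatch is harmless.** Largely so. A constant factor changes reported HOMA levels but not P values, log-scale comparisons or correlations. A reader might infer that the reported HOMA values will be 1,000 times too large. The article shows only that the units are mixed, not which unit will be entered.

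**Conclusion.** The point holds in limited form. Matsuda and MISI, two of seven secondary-outcome indices, cannot be computed as Table 3 defines them, because 75% of the averaging window has no insulin data. This conclusion rests only on the article's text and needs no assumption. MISI has a second weakness that added insulin would not cure: its slope rests on two glucose points at best and is undefined when glucose does not fall after 30 minutes.

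No percentage bias can be attached to this. The illustrated figures run from −9% to +34% for Matsuda and from −17% to +80% for MISI under assumed inputs. They concern index levels, whereas the outcome is a between-group difference in change, for which no bias was computed.

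Severity is should-fix: the definitions are wrong as written and cannot be rescued after the visits, but they affect secondary indices in a 34-person feasibility trial. The unit mismatch is minor.

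**What to change.** Before recruitment, choose one of two routes.

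- **Add the assay.** Measure insulin at the existing 120-minute venous draw at baseline and at 8 weeks. State how the 2-hour mean is formed from 0, 30 and 120 minutes. Report Matsuda as a sparse three-point version. Drop MISI, or label it a two-point approximation and say how participants without a fall in glucose after 30 minutes are handled.
- **Do not add the assay.** Drop both indices, or redefine and rename them as 0-30 minute measures.

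Under either route, reconcile the insulin unit in Table 3 for HOMA-B and HOMA-IR. The disposition index value does not depend on it.

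**Cost.** With full attendance, at least 34 × 2 = 68 assays, provided baseline samples are held until eligibility is known. Baseline insulin is taken at step 3 screening, before eligibility is established, so assaying everyone screened costs more. At an assumed 30% screening yield, with all eligible people enrolled, the count is 34/0.30 ≈ 113 at baseline plus 34 at 8 weeks, or about 147. The article describes insulin samples as additional to the glucose samples, so a separate tube at 120 minutes may be needed; no extra sampling time is. The second route costs only a text change.

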##### Indices of ß Cell Function and Insulin Resistance

Table 3 provides details on the indices of ß Cell function and insulin resistance derived from glucose and insulin levels. Early-phase insulin secretion will be assessed using the insulinogenic index [54], while total ß cell function with be evaluated with the oral disposition index [55] and homeostatic model assessment of ß cell function [56]. Whole-body insulin resistance will be determined using the Matsuda index [57] and homeostatic model assessment of insulin resistance [56], while tissue-specific insulin resistance will be assessed with the hepatic insulin resistance index [58] and muscle insulin sensitivity index [58].

**Table 3 table3:** Indices of ß-cell function and insulin resistance.

ß cell function or IR^a^ and components		Indices	Formula
**ß cell function**			
	Early-phase insulin secretion:	IGI^b^ [54]	(I_30_^c^–I_0_^d^)/(G_30_^e^–G_0_^f^)
	ß cell function	DI_O_^g^ [55]	([ I_0-30_/ G_0-30_]×[1/I_0_]) I0 in µU/l G0 in mmol/l
	ß cell function	HOMA-B^h^ [56]	(20×I_0_)/(G_0_–3.5) I0 in µU/l G0 in mmol/l
**Insulin resistance**			
	Whole-body insulin sensitivity	Matsuda index [57]	10,000 /√((G_0_×I_0_)×(G_mean_^i^×I_mean_^j^))
	Insulin resistance	HOMA-IR^k^ [56]	(I_0_×G_0_)/22.5 I0 in µU/L G0 in mmol/l
	Hepatic insulin resistance	HIRI^l^ [58]	(G_0_–G_30_[AUC^m^]×I_0_-_30_[AUC]) G0 in mg/dl I0 in µU/ml
	Muscle insulin resistance	MISI^n^ [58]	(dG/dt^o^)/Ī^p^

^a^IR: insulin resistance.

^b^IGI: insulinogenic index.

^c^I_30_: mean insulin at 30 minutes during the oral glucose tolerance test.

^d^I_0_: mean insulin at 0 minutes during the oral glucose tolerance test.

^e^G_30_: mean glucose at 30 minutes during the oral glucose tolerance test.

^f^G_0_: mean glucose at 0 minutes during the oral glucose tolerance test.

^g^DI_O_: oral disposition index.

^h^HOMA-B: homeostatic model assessment of ß cell function.

^i^G_mean_: mean glucose during the 2-hour oral glucose tolerance test.

^j^I_mean_: mean insulin during the 2-hour oral glucose tolerance test.

^k^HOMA-IR: homeostatic model assessment of insulin resistance.

^l^HIRI: hepatic insulin resistance index.

^m^AUC: area under the curve during the first 30 minutes of the oral glucose tolerance test.

^n^MISI: muscle insulin sensitivity index.

^o^dG/dt: slope of the regression line from the peak of the plasma glucose curve to its nadir (mmol/L/min).

^p^Ī: mean insulin concentration over the 2-hour duration of the oral glucose tolerance test (pmol/L).

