### Step 3: Screening (via In-Person Clinic Visits)

Individuals meeting the step 2 criteria will be invited to visit the GCRC at Emory University Hospital after fasting overnight for a minimum of 8 hours [29]. During the visit, participants will complete standard questionnaires to collect sociodemographic information (education, occupation, and marital status) [34,35] and details on alcohol consumption [34,35] and dietary intake [36]. Additionally, physical measurements will be conducted using standardized instruments in accordance with the World Health Organization’s STEPwise approach to noncommunicable disease risk factor surveillance (STEPS) protocol [37]. Following these assessments, individuals will undergo an oral glucose tolerance test (OGTT) and provide blood samples for insulin. Individuals diagnosed with i-IFG, defined by the American Diabetes Association criteria as FPG between 100-125 mg/dL and 2-hour plasma glucose<140 mg/dL [29], will be deemed eligible to participate in the study. Individuals without i-IFG will be excluded from further participation in the study. They will receive a summary report of their test results and general healthy lifestyle advice and will be referred to their general practitioner if they have IGT or undiagnosed diabetes for further management.

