### Statistical Analysis

#### Quantitative Research

##### Objective 1

Continuous variables will be summarized using either mean (SD) or median (IQR), depending on their distribution, which will be visually assessed through histograms. Categorical variables will be presented as counts (n) and percentages (%).

##### Objective 2

The analyses will adhere to the “intention-to-treat” principle. Between-group differences in changes in continuous variables from baseline to 8 weeks will be analyzed using mixed-effects linear regression models, while categorical variables will be assessed with log-binomial models. Skewed variables will be log-transformed prior to analysis. Fixed effects will include the study group (intervention vs control), timepoint (follow-up vs baseline), and the interaction between the study group and timepoint. Random effects will be specified for participants to account for the correlation between repeated measurements on the same individual. The *P* value for the study group-by-timepoint interaction will be used to evaluate the difference in changes between the study groups. The correlation between changes in fasting glucose levels and the indices from baseline to 8 weeks will be assessed using either Pearson or Spearman correlation coefficients, depending on the nature of the data distribution. Mixed-effects linear regression models will be used to compare CGM metrics between study groups, adjusting for baseline values. These models will also examine within-participant differences in CGM metrics between exercise and non-exercise days. Statistical significance will be considered with a 2-sided *P* value<.05 with no adjustments for the multiplicity of comparisons. All analyses will be conducted using Stata (version 18.0; StataCorp LLC).

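### Glucose drawn only at 0, 30 and 120 minutes cannot supply the peak-to-nadir slope in the muscle insulin sensitivity index (MISI); a 60-minute peak or 90-minute nadir understates it by at least one third

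*Protocol article*

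**What the plan says.** Table 3 (under Indices of ß Cell Function and Insulin Resistance) gives MISI as (dG/dt)/Ī. Footnote o defines dG/dt as the "slope of the regression line from the peak of the plasma glucose curve to its nadir (mmol/L/min"), with no minus sign or absolute value. Footnote p defines Ī as the "mean insulin concentration over the 2-hour duration of the oral glucose tolerance test (pmol/L").

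The Biochemical Measures section fixes the sampling: "Venous blood samples will be collected at 0, 30, and 120 minutes after ingesting a 75-g oral glucose load". Table 1 gives the same times for the glucose tolerance test, "0, 30, and 120 minutes". Continuous glucose monitoring is a separate outcome and is not named as the source of this plasma curve.

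MISI is presented as a tissue-specific measure. It belongs to the indices listed under Secondary Outcomes, and under Statistical Analysis, Objective 2, changes in the indices are correlated with changes in fasting glucose. The same paragraph says "Skewed variables will be log-transformed prior to analysis".

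**The concern.** The definition needs the shape of the glucose curve after its peak, and the schedule does not observe that shape. A peak after 30 minutes or a nadir before 120 minutes goes unrecorded, and the nominal regression is then usually a line through two points with no residual degrees of freedom. This is a conflict between two things the article states, not a detail that it leaves to a fuller document.

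At stake is what a change in the index would mean. The error depends on when the peak and nadir occur. If the intervention shifted that timing, the computed slope could move even though the peak-to-nadir slope did not, or could move the opposite way, and the result would be reported as an effect on muscle.

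**Working it through.** **Inputs from the article.** Glucose at 0, 30 and 120 minutes (Biochemical Measures; Table 1). Slope from peak to nadir (Table 3, footnote o). Eligibility requires "FPG between 100-125 mg/dL and 2-hour plasma glucose<140 mg/dL" (Step 3 screening). The article gives no MISI value and no peak-timing data, so there is no stated figure to reproduce.

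**Assumptions.** Nadir means the lowest value at or after the peak. The comparison schedule is 0/30/60/90/120 minutes. All curves below are assumed. They are in mg/dL, and the ratios do not depend on units.

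**What the rule returns on three samples.**
- Highest at 30 minutes: the only later point is 120, so the slope is (G120 − G30)/90.
- Highest at 120 minutes: no later point, so no slope. At baseline this needs G30 below G120, which must itself be below 140 mg/dL. No such limit applies at 8 weeks.
- Highest at 0 minutes: the line starts at 0.

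**Bound for a peak P at 60 and nadir at 120.** A least-squares line through three equally spaced points (60, 90, 120) has rate of fall (P − G120)/60. The three-sample rate is (G30 − G120)/90. The ratio is (60/90) × (G30 − G120)/(P − G120). Because G30 ≤ P, it is at most 60/90 = 0.67.

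**Bound for a peak at 30 and nadir at 90.** The full-curve rate is (G30 − G90)/60 and the three-sample rate is (G30 − G120)/90. Because G120 ≥ G90, the ratio is again at most 0.67.

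Both losses are therefore at least one third, whatever the glucose values. By the same argument, a peak at 90 with nadir at 120 gives at most 30/90 = 0.33.

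**Assumed curves (slopes in mg/dL/min).**

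| Curve at 0/30/60/90/120 | Peak, nadir (min) | Five-sample slope | Three-sample slope | Ratio |
|---|---|---|---|---|
| 110/165/140/120/115 | 30, 120 | −0.567 | −0.556 | 0.98 |
| 110/160/165/140/120 | 60, 120 | −0.750 | −0.444 | 0.59 |
| 110/150/170/145/120 | 60, 120 | −0.833 | −0.333 | 0.40 |
| 110/145/180/150/125 | 60, 120 | −0.917 | −0.222 | 0.24 |
| 110/165/160/125/130 | 30, 90 | −0.667 | −0.389 | 0.58 |
| 110/165/140/120/121 | 30, 90 | −0.750 | −0.489 | 0.65 |
| 108/130/150/140/135 | 60, 120 | −0.250 | none | – |

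On an assumed grid (G0 100–125, G30 120–200, peak up to 220, G120 80–135 mg/dL), the ratio for a 60-minute peak had median 0.39 and range 0.03 to 0.64. About 11% of grid cells had no 30-to-120 line. The grid is an unweighted set of combinations, not a patient population.

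**A shift in timing.** Suppose 110/150/170/145/120 (peak at 60) becomes 110/170/150/135/120 (peak at 30). The three-sample rate of fall rises from 30/90 = 0.33 to 50/90 = 0.56, up 67%. The five-sample rate falls from 50/60 = 0.83 to 0.55, down 34%. The two versions of the index move in opposite directions.

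**Sign.** Of the six orderings of three distinct values, four give a slope, and it is negative each time; the other two give none. Mean insulin is positive, so MISI as written is negative wherever a slope exists.

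**The case against.** The strongest reply has four parts.

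*The size rests on invented curves.* Largely right. A reader might infer from the examples that the loss is about 40–60% whenever the peak is at 60 or the nadir at 90. That does not follow: the curves above with those features give ratios from 0.24 to 0.65. Only the one-third minimum is free of assumed glucose values, and a 30-minute peak with a 120-minute nadir loses almost nothing. It would likewise be too strong to say the slope is always the 30-to-120 line, because the highest sample can be at 0 or 120.

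*No between-group bias is shown.* Also right. If peak timing were similar in both arms and at both visits, the main effect would be attenuation. The opposite-direction example shows what can happen, not what will. The article offers no evidence that the intervention shifts peak timing.

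*The sign is a convention.* A reader might infer that the negative sign invalidates the analysis or reverses the finding. It does not: a consistent sign flip leaves the untransformed group-by-time test and the size of any correlation unchanged. The logarithm problem arises only if MISI is skewed, which is unknown. What stands is a wording matter: an index named for sensitivity, listed under muscle insulin resistance, gets lower as glucose falls faster.

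*The denominator fails anyway.* The article says "blood samples for insulin will be obtained at 0 and 30 minutes after glucose load ingestion", so a 2-hour mean insulin is not available either. That is true, and it means MISI cannot be computed as defined on a second ground. It does not dispose of this point, because complete insulin sampling would leave the glucose slope unrepaired.

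**Conclusion.** The point holds as a mismatch between the MISI numerator and the glucose schedule. Following the plan yields a two-point line, or no slope, in place of a peak-to-nadir regression. Against five-sample testing, the loss is at least one third for a 60-minute peak with a 120-minute nadir, or a 30-minute peak with a 90-minute nadir. It is larger on many assumed curves and negligible for a 30-minute peak with a 120-minute nadir. This rests on reading nadir as the lowest value at or after the peak. How often the affected shapes occur, and whether they would differ by group, cannot be judged from the article.

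The consequence is limited. MISI is one of seven indices in Table 3, in a 34-person proof-of-concept trial whose primary outcomes are feasibility and acceptability. The Introduction attributes muscle insulin resistance to isolated impaired glucose tolerance, not to isolated impaired fasting glucose. The correction should still be made, because the index would otherwise be reported as evidence about muscle that these samples cannot provide.

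**What to change.** Remove MISI and the muscle-specific claim: delete its row and footnotes n, o and p from Table 3, delete the muscle clause in the paragraph above that table, and state that MISI is not among the indices in the secondary outcomes or in the Objective 2 correlations.

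Alternatively, keep only a descriptive glucose-fall measure, defined as (G30 − G120)/90 with positive values meaning a faster fall, and say that it is not interpreted as muscle insulin sensitivity. It takes negative values when the 120-minute value is the higher, so it should be analysed without log transformation. Stating the direction also settles the sign question.

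Either change is wording only and needs no extra blood draws. The cost is one secondary index. Keeping MISI as defined would instead require more glucose and insulin samples. Because the baseline glucose tolerance test is also the step 3 screening test, those draws would fall on people who turn out to be ineligible as well.
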